## Abstract

**Background:**

Besides the beneficial health effects of being active, running is associated with a risk of sustaining injuries. Runners need to change their behavior to increase the use of effective measures and subsequently reduce the number of running-related injuries.

**Objective:**

The RunFitCheck intervention was developed according to an evidence- and practice-based approach to stimulate injury-preventive behavior among novice runners. This paper describes the study design in detail.

**Methods:**

A randomized controlled trial with a follow-up period of 5 months will be conducted. The participants will be novice runners. At enrollment, participants will be asked to report injury-preventive measures they usually take during their running activities. After completing the enrollment questionnaire, participants will be randomized to intervention and control groups. The intervention group will have access to the RunFitCheck intervention; the control group will perform their running activities as usual. Participants will be asked to report retrospectively in detail what they have done regarding injury prevention during their running activities at 1, 3, and 5 months after enrollment. Descriptive analyses will be conducted for different baseline variables in the intervention and control group. Relative risks and 95% CIs will be used to analyze behavioral changes according to the intention-to-treat principle.

**Results:**

The project was funded in 2016 and enrollment was completed in 2017. Data analysis is currently under way and the results are expected to be submitted for publication in 2019.

**Conclusions:**

To nullify the negative side effects of running, prevention of training errors is desirable. As the use of injury prevention measures is not compulsory in running, a behavioral change is necessary to increase the use of effective injury-preventive measures and to prevent running-related injuries.

**Trial Registration:**

Netherlands Trial Register NTR6381; http://www.trialregister.nl/trialreg/admin/rctview.asp?TC=6381 (Archived by WebCite at http://www.webcitation.org/736Xjm5jv)

**International Registered Report Identifier (IRRID):**

RR1-10.2196/9708

## Introduction

Running is one of the most popular ways to exercise in the Netherlands, with 2.1 million people running on a regular basis [1]. In addition to beneficial health effects of being active, running is associated with a high risk of musculoskeletal injuries. The incidence of running-related injuries (RRIs) is reported to range from 3-59 injuries per 1000 exposure hours [2-4], with most RRIs occurring in the knee, followed by the calf, Achilles tendon, and shin [5].

Risk factors for RRIs have been extensively investigated, but evidence remains contradictory and inconclusive. A history of injury in the past 12 months is reported to be the main risk factor for RRIs [6,7]. Especially, novice runners are at a high risk of sustaining an RRI, while according to running experts, half of the RRIs are related to training errors [3]. Consequently, these injuries could be prevented since modifying the training load should be easily realizable [8,9]. However, modifying one’s training load and inherently preventing training errors might be easier said than done. A behavioral change among runners is necessary to increase injury-preventive behavior and, subsequently, the use of preventive measures. To our knowledge, 2 interventions aimed at runners to promote preventive behavior and reduce RRIs have been developed earlier [10,11]. Adriaensens et al [10] developed a tailored Web-based injury prevention intervention: a website with informational videos about the etiology and mechanisms of RRIs combined with injury-preventive advice and a Web-based questionnaire that allowed the website to provide tailored feedback based upon a series of predefined questions that created a personal risk profile of the user. Short-term (3 months) effects of the intervention (measured in recreational runners after a visit to the website of 30 minutes) were demonstrated on determinants and actual performance of sports injury behavior. Hespanhol et al [11] evaluated the effectiveness of adding Web-based tailored advice to general advice on the prevention of RRIs and determinants as well as actual preventive behavior in Dutch trail runners. Trail runners in the intervention group received specific advice tailored to their RRI status (no injury, no substantial RRI, or substantial RRI). In that study, no effect was observed on determinant and actual preventive behavior; however, RRIs were prevented [11]. Tailored Web-based intervention can thus be promising in promoting preventive behavior among runners and even prevent RRIs. The intervention developed by Adriaensens et al (Dutch Consumer Safety Institute) [10] was effective, but the Web-based questionnaire for tailored feedback was time-consuming. Therefore, the Dutch Consumer Safety Institute developed the RunFitCheck intervention to stimulate injury-preventive behavior among novice runners without the associated time burden. The next step is to evaluate its effect on injury-preventive behavior among novice runners. This paper describes the study design in detail.

## Methods

### Objective and Hypothesis

The objective of the study is to evaluate the effectiveness of the developed RunFitCheck intervention (in Dutch) to promote injury-preventive behavior among novice runners. The hypothesis in this study is that the developed intervention will lead to 10% difference in favorable injury-preventive behavior in the intervention group compared with the control group.

### Study Design

The Consolidated Standards of Reporting Trials statement was followed to describe the design of the study [8]. This statement is a checklist intended to improve the quality of reports of randomized controlled trials. A randomized controlled trial with a follow-up period of 5 months will be conducted (Figure 1). The study is registered in the Dutch Trial Registry (Netherlands Trial Register Number NTR6381).

**Figure 1 figure1:**
[figure not shown]
Flowchart of participants of the randomized prospective controlled trial.

### Ethics, Consent, and Permissions

The study protocol has been approved by the Medical Ethics Review Committee of the Academic Medical Center Amsterdam, the Netherlands (W16_335 # 16.417). Participants willing to participate in the study will give their informed consent prior to the start of the enrollment questionnaire. The start screen of the enrollment questionnaire will be used to obtain informed consent from the participants. This screen will contain information about the study, use of the data gathered, and rights of the participants in this study. If participants agree to participate in this study after they have read the information, they will have to tick a box to give their informed consent. When participants tick the informed consent box, they are able to continue to the first question of the enrollment questionnaire. The flowchart of the participants is presented in Figure 1.

### Participants and Recruitment

The group of participants will consist of novice runners. The inclusion criteria are being aged 18 years and older, considering oneself as a beginner, a slightly experienced runner, or a rather experienced runner, and having less than one year of running experience when a runner considers oneself as an experienced or very experienced runner. Participants do not have to be a member of a running club. Participants will be recruited via social media networks (Facebook, websites, Twitter, LinkedIn, and newsletters) of the participating organizations (Dutch Consumer Safety Institute, Runner’s World, and Royal Dutch Running Association [RDRA]) and will be able to preregister for the study in the 2 months prior to the start of the study.

### Sample Size and Allocation

In this study, the aim is to increase injury-preventive behavior by 10% in the intervention group. In previous literature, 12.6% increase in injury-preventive behavior (in this case, the inclusion of a warm-up) was found during a 3-month intervention [10]. To achieve 80% power with a significance level of.05, the sample size calculation revealed that 384 participants per study group are needed in this study. Taking into account a response rate of 85% and a dropout rate of 10% over the 5-month follow-up period, a total of 1000 participants will be approached in this study. Eligible participants will be simultaneously allocated at random to the intervention or control group after study commencement, using a computerized random number generator (the Aselect function in Excel). No restrictions will be imposed for the allocation; simple randomization will be performed. All steps in the randomization process will be done by the principal researcher.

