### Statistical Analysis

Descriptive analyses (mean [SD], frequency, and range) will be conducted for the different baseline variables in both study groups. To evaluate the success of the randomization, baseline variables will be analyzed for differences between the intervention and control group (chi-square test, independent *t* test, and Mann-Whitney test).

Relative risks (RRs) and a 95% CI will be used to analyze behavioral change according to the intention-to-treat analyses: (1) using a (personalized) training schedule, (2) performing strength and technique exercises, (3) performing a warm-up. Participants who do not execute a certain injury-preventive measure at study commencement will be selected for analysis, since among these participants, most behavioral change can be expected. If there are any differences in descriptive characteristics at baseline (eg, differences in sex, age, or running experience), subanalyses for sex, different age categories, etc will be performed.

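### The 80% power is stated for 384 retained runners per group whatever their baseline behaviour, but each relative risk uses only runners not doing that behaviour at baseline, so the figure is tied to no planned analysis

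*Protocol article*

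**What the plan says.** - **Size.** Protocol article, Sample Size and Allocation, reports that "the sample size calculation revealed that 384 participants per study group are needed in this study". The target behind this number is put as "To achieve 80% power with a significance level of.05".
- **Effect.** The same section says "the aim is to increase injury-preventive behavior by 10% in the intervention group". Objective and Hypothesis puts it as a "10% difference in favorable injury-preventive behavior in the intervention group compared with the control group". Neither says whether the 10% refers to all runners or to those not yet performing the behaviour. The only supporting figure is that a "12.6% increase in injury-preventive behavior (in this case, the inclusion of a warm-up) was found during a 3-month intervention"; no control-group rate is given with it.
- **Allowances.** The outcome of the calculation is that "a total of 1000 participants will be approached in this study". The only basis given for the step up from 384 per group is this: "Taking into account a response rate of 85% and a dropout rate of 10% over the 5-month follow-up period". Recruitment of Participants treats the 1000 as the number to enrol. No allowance is made for runners who already perform a behaviour.
- **Eligibility.** Participants and Recruitment sets criteria on age and running experience only. A runner who already does any of the three behaviours can enter.
- **Analysis set.** Statistical Analysis plans a relative risk with 95% CI for each of three behaviours (training schedule, strength and technique exercises, warm-up), and adds: "Participants who do not execute a certain injury-preventive measure at study commencement will be selected for analysis".

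**The concern.** The sizing and the analysis describe different sets of people. The sizing counts every runner who stays in follow-up. The analysis drops, behaviour by behaviour, everyone who already performs that behaviour. The article expects such runners to exist, since otherwise the selection rule would have no purpose.

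Two things follow. The number analysed is smaller than 384 per group by an amount that the article does not state. The comparison also becomes uptake among people who start at zero, whose control rate need not resemble the rate behind 384. One power figure then stands for three analyses that may each have a different power.

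The stake is how results are read. The article makes a 10% change its sign of efficacy, so a result without a clear difference will be judged against the stated 80%. If a behaviour's analysed set does not deliver that power, the reassurance is false.

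**Working it through.** **1. Can 384 be reproduced?** Inputs from the article: power 80%, significance level .05, a 10% difference. Sidedness and the control rate are not stated. I assume a two-sided test, 1:1 allocation and 10 percentage points.

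Unpooled formula: n = (1.960 + 0.842)² × [p1(1 − p1) + p2(1 − p2)] / (p1 − p2)².
- 40% v 50%: 7.849 × (0.24 + 0.25) / 0.01 = 384.6. By symmetry, 50% v 60% gives the same.
- With pooled variance under the null, 40% v 50% gives 388, and exactly 384 arises at about 38% v 48% or 52% v 62%.
- Within 3%, the pooled formula fits 384 for control rates of about 34% to 56%.
- One-sided tests do not reach 384 at any control rate (at most 309, or 328 with continuity correction). Nor does a 12.6-point difference (at most 262).

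So 384 is consistent with a two-sided 10-point difference at a mid-range control rate. That rate is worked back from 384 and is not stated in the article.

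**2. Does the step to 1000 leave room for the selection?**
- Forward: 2 × 384 = 768; 768 / (0.85 × 0.90) = 768 / 0.765 = 1004.
- Backward: 1000 × 0.765 / 2 = 382.5 per group.

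The two stated allowances account for the whole difference between 768 and 1000. Hence 384 is the number per group left after non-response and dropout, whatever the baseline behaviour. It cannot also be the number of non-performers unless f = 1.

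**3. Number in each analysis.** n = 384 × f per group: 307 at f = 0.8, 230 at 0.6, 192 at 0.5. Running as Usual also excludes control participants who visited the website. That lowers the control number further and is likewise not allowed for; it is left out of the figures below.

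**4. Power, reading A: 10 points within the analysed set.** Power = Φ[(d − 1.960 × SE0) / SE1], where SE0 uses the pooled rate and SE1 the two separate rates. Both f and the control rates are assumptions.

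| Control v intervention | f = 1 | f = 0.8 | f = 0.6 | f = 0.5 |
|---|---|---|---|---|
| 40% v 50% | 80% | 70% | 58% | 50% |
| 30% v 40% | 83% | 74% | 61% | 54% |
| 20% v 30% | 89% | 82% | 70% | 62% |
| 10% v 20% | 97% | 94% | 85% | 79% |
| 5% v 15% | above 99% | 99% | 95% | 91% |

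At f = 0.25 (96 per group) and 40% v 50%, power is 28%.

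**5. Power, reading B: 10 points over all runners, all of it among non-performers.** The difference in the analysed set is then 10/f points: 12.5 at f = 0.8, 16.7 at 0.6, 20 at 0.5. With 40% control uptake among non-performers, power is 88%, 95% and 98%. With lower control uptake it is higher, for example 99.9% at 10% uptake and f = 0.5.

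**6. What it would take to keep 384 non-performers per group.** Total enrolment would be 1004 / f: about 1255 at f = 0.8, 1674 at 0.6 and 2008 at 0.5, against 1000 planned. This only shows the size of the gap. It is not a proposal to recruit.

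**The case against.** The strongest case against is that no loss of power has been shown. The article gives neither f nor a control rate. Few non-performers in the control group may take up a behaviour unprompted, and a 10-point difference is easier to detect at low rates: at 5% v 15%, half the sample still gives 91%. On reading B, 384 is even conservative. The article's wording of the 10% allows that reading. All of this stands. A reader might infer that every analysis is underpowered, or that warm-up is so common that its analysis must be. The documents support neither: the only warm-up figure is an increase, not a prevalence. A reader might also take 40% v 50% as the trial's planning rates, or 384 as the number randomised. The first is back-calculated, and the second is about 500 per group.

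A second objection is that an article may leave the assumed rates to a fuller document. That holds for the rates, and their absence is not the point here. The two statements that do not fit, the sizing with its allowances and the selection rule, both stand in this article.

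Third, confidence intervals are planned, and a small analysed set would show as a wide interval. This softens the harm but does not make the stated power correct.

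Fourth, enrolment is complete and analysis is under way, so a design-stage correction is no longer possible. This limits the remedy to restating the figure.

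**Conclusion.** The point holds as a mismatch between the sizing and the analysis set. The 80% is stated for 384 retained runners per group of any baseline behaviour, and the 1000 leaves no margin for the later selection. Every planned relative risk is computed in a subset of about 384 × f per group. The single figure would be the power of a given analysis only if nobody performed that behaviour at baseline, or if the unstated values happened to offset each other.

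Over the assumed values shown, the actual power runs from about 28% (40% v 50%, f = 0.25) to nearly 100% (effect concentrated among non-performers). If the 10 points apply within the analysed set at rates consistent with 384, power falls below 80% as soon as f is clearly below 1. If control uptake is low, or the 10 points refer to all runners, it need not fall. The direction therefore cannot be settled from the article, and a general loss of power should not be claimed. These results assume a two-sided test, equal groups and no loss from excluded control visitors.

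**What to change.** Restate the power for the sets that are analysed:

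1. Say whether the 10% applies to all runners or to baseline non-performers, and that it is in percentage points if so meant.
2. For each of the three behaviours, give the assumed control uptake among non-performers, the number of non-performers per group and the resulting power. Take the number from the enrolment answers pooled over both groups, without using outcomes by arm. The assumed uptake should not come from the trial's own follow-up results.
3. Do not claim 80% power for a behaviour whose set does not deliver it.

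Since analysis is under way, the text should also say when the restatement was made.

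The cost is a few lines in the protocol or analysis plan and one calculation on baseline data already collected. No extra recruitment is needed, and the choice to study uptake among non-performers can stay. The only downside is that the stated power may become less favourable for some behaviours.

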### Procedures

Upon enrollment, participants will be asked to report the injury-preventive measures they usually take before or during their running activities. Participants’ demographic characteristics, including their contact email address, sex, age, running experience, running motivation, physical fitness, current injuries and physical complaints, and injury-preventive measures, will also be collected upon enrollment via a Web-based enrollment questionnaire (Table 1).

**Table 1 table1:** Overview of research topics per questionnaire in this study.

Research topics	Enrollment questionnaire	At 1 month after enrollment	At 3 months after enrollment	At 5 months after enrollment
Age	Present	N/A^a^	N/A	N/A
Sex	Present	N/A	N/A	N/A
Sports participation other than running	Present	Absent	Absent	Absent
Running motivation	Present	Absent	Absent	Absent
Running experience (in months or years)	Present	Absent	Absent	Absent
Level of running (novice, seminovice, experienced, etc)	Present	Absent	Absent	Absent
Running frequency per week	Present	Present	Present	Present
Physical fitness	Present	Present	Present	Present
Risk perception	Present	Present	Present	Present
Injury-preventive behavior	Present	Present	Present	Present
Running-related injuries	Present	Present	Present	Present
Physical complaints	Present	Present	Present	Present

^a^N/A: not applicable.

All personal information and contact information from the participants will be handled by the principal researcher. This researcher will export the data from SurveyMonkey and store it in a password-protected drive. Participant names will be replaced with numbers and stored as reidentifiable data. The data with participant numbers will be utilized in the statistical analyses. Upon the conclusion of the data collection period, the questionnaire and associated responses will be deleted from SurveyMonkey.

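### The whole cohort is allocated in one draw with baseline behaviours already recorded, yet the draw is not stratified and no adjustment is named: a small improvement left unused, not an error

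*Protocol article*

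**What the plan says.** Four parts of the Protocol article bear on this point.

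- **Timing.** The abstract says: "After completing the enrollment questionnaire, participants will be randomized to intervention and control groups". Procedures (Table 1) lists injury-preventive behaviour, sex, age, running experience and running level among the enrolment items.
- **Method.** Under Sample Size and Allocation: "Eligible participants will be simultaneously allocated at random to the intervention or control group after study commencement, using a computerized random number generator", the tool being "the Aselect function in Excel". The section continues: "No restrictions will be imposed for the allocation; simple randomization will be performed".
- **Who does it.** The same section says: "All steps in the randomization process will be done by the principal researcher". Procedures adds: "All personal information and contact information from the participants will be handled by the principal researcher".
- **Analysis.** Statistical Analysis plans relative risks with 95% confidence intervals for three behaviours (training schedule, strength and technique exercises, warm-up). Each is restricted to participants who do not perform that behaviour at the start. No covariate adjustment is named. Baseline variables are tested between groups, and differences lead to subanalyses by sex, age category and the like.

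**The concern.** Trials often use simple randomisation because participants arrive one at a time and short blocks could make the next assignment predictable. Neither reason applies here. Everyone is allocated at one moment, with covariates in hand, so a stratified draw would need no extra visit, staff or system.

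The variables that would serve as strata are also those that define the analysis subsets. Within the subset for one behaviour, that behaviour's baseline status is the same for everyone. The numbers per arm, and the mix of the other two behaviours, are left to chance. The only stated response to chance imbalance is testing followed by subanalyses. Splitting the sample gives several smaller comparisons and does not correct the main estimate. At stake is some precision in each subset and a cleaner rule for handling baseline differences. Validity is not at stake.

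**Working it through.** **1. The plan's own figures.** The stated setting is "To achieve 80% power with a significance level of.05". The target is a 10% increase, read as 10 percentage points; the test is assumed two-sided. The control rate is not stated. At an assumed 50% versus 60%, the unpooled formula gives 384.6 per group and the pooled formula 388, so the stated 384 reproduces. For the total: 2 × 384 = 768, and 768 / (0.85 × 0.90) = 1003.9, in line with 1000.

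**2. Arm size.** With N = 1000 and probability 0.5, the 95% range for one arm is 469 to 531. Efficiency relative to an equal split is 4 × 0.469 × 0.531 = 99.6%. With 1000 × 0.85 × 0.90 = 765 analysed, power for 50% versus 60% is 79.5% for an equal split and 79.4% at the 469/531 limit. The loss is about 0.1 point.

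**3. Imbalance in another behaviour.** For a factor of prevalence q, the 95% limit of the between-arm difference is 1.96 × √(4q(1 − q)/N). With q = 0.5 (assumption):

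| N | 95% limit of difference | Arm split at 95% limit | Efficiency of split |
|---|---|---|---|
| 1000 | ±6.2 points | 469/531 | 99.6% |
| 300 | ±11.3 points | 133/167 | 98.7% |
| 200 | ±13.9 points | 86/114 | 98.0% |

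The article does not state the subset sizes; 300 and 200 are illustrations.

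**4. What that imbalance does to the outcome.** If the outcome rate differs by d between those who do and do not perform another behaviour, the chance shift is d × imbalance. At N = 300 and d = 10 to 30 points (assumption), the 95% limit is 0.10 × 11.3 = 1.1 to 0.30 × 11.3 = 3.4 points. At N = 200 it is 1.4 to 4.2 points. An ordinary confidence interval already allows for this, so it is lost precision and not bias.

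**5. Gain from accounting for it.** The share of outcome variance explained by one binary factor is d² × q(1 − q) / (p(1 − p)), where p is the outcome rate. With q = p = 0.5 this is d²: 0.10² = 1% to 0.30² = 9%. The interval on the difference scale narrows by 1 − √0.99 = 0.5% to 1 − √0.91 = 4.6%.

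**6. How often the test-and-split rule would fire by chance.** With k independent tests at 0.05, the chance of at least one significant result is 1 − 0.95^k: 23% for k = 5 and 40% for k = 10. The number of tests, their independence and the 0.05 trigger are assumptions.

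**The case against.** The strongest reply is that nothing here is wrong. Simple randomisation of about 1000 people is unbiased, the chance of a 45/55 split or worse is 0.2%, and allocating everyone together after enrolment prevents enrolment from being steered by a foreseen assignment. All of this stands, and it is why the point is minor.

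It can also be said that stratifying on the three behaviours would not balance sex, age or running experience, the examples the plan gives as triggers for subanalyses. That stands too. Stratification alone would leave those triggers in place, so the change to the analysis matters more than the change to the draw.

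Two stronger readings are tempting, and the documents support neither.

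- **That the allocation cannot be reproduced, or that a redraw would leave no trace.** A reader might infer this from a spreadsheet function used by one person who also holds identities and answers. The article does not say whether the list was fixed, saved or archived, and an article commonly leaves such detail to the full protocol. How the spreadsheet function behaves is not in the documents either.
- **That a 5-point baseline difference in a behaviour uses up half of the 10-point target effect.** With 500 per arm and 50% prevalence, such a difference has an 11% chance per behaviour (standard error √(0.5/500) = 3.16 points). But within its own analysis subset the behaviour is constant, so the difference changes only how many people enter each arm: about 237.5 versus 262.5. Efficiency is 4 × 237.5 × 262.5 / 500² = 99.75%. A baseline difference of this kind is not on the same footing as an outcome effect.

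**Conclusion.** The point holds as a small, nearly free improvement. The plan has the whole cohort and its baseline behaviours available at one draw, rules out any restriction, and then analyses baseline-defined subsets with no adjustment named. The benefit forgone is about 0.1 point of power from overall arm size, 1% to 2% of efficiency from uneven splits at the 95% limit in subsets of 300 or 200, and roughly 1% to 9% of variance for one of the other two behaviours. These figures rest on assumed subset sizes, 50% prevalence, a 50% outcome rate, and an outcome difference of 10 to 30 points across the other behaviour. Simple randomisation remains valid, and no result would be invalid on this account.

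**What to change.** **If the draw is still to be made:** randomise in permuted blocks within the 2 × 2 × 2 = 8 cells of baseline status on the three behaviours. State beforehand how an answer of not applicable is classed. Make the draw in one scripted run with a recorded seed, and lock the list before access emails are sent.

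**In the analysis:** adjust each relative risk for baseline status of the other two behaviours, for example by Mantel–Haenszel weighting over their four cells or Poisson regression with robust variance. Prespecify this, and use it in place of subanalyses triggered by baseline differences.

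The Results section reports that enrolment was completed in 2017 and that analysis is under way. If allocation has already taken place, only the adjustment applies. It should be fixed in writing before outcomes are compared by group; if that comparison has already been made, the date of the decision should be reported.

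**Cost:** a short script and one archived file for the draw, and a sentence or two of text for the analysis. The adjustment needs no new data, because the behaviours are already collected at enrolment.
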